# TRACE (Routine posTsuRgical Anesthesia visit to improve patient outComE): a prospective, multicenter, stepped-wedge, cluster-randomized interventional study

**DOI:** 10.1186/s13063-018-2952-5

**Published:** 2018-10-26

**Keywords:** Anesthesiology, Postsurgical complications, Failure-to-rescue, In-hospital mortality, Stepped-wedge cluster randomized trial

## Abstract

**Background:**

Perioperative complications occur in 30–40% of non-cardiac surgical patients and are the leading cause of early postoperative morbidity and mortality. Regular visits by trained health professionals may decrease the incidence of complications and mortality through earlier detection and adequate treatment of complications. Until now, no studies have been performed on the impact of routine postsurgical anesthesia visits on the incidence of postoperative complications and mortality.

**Methods:**

TRACE is a prospective, multicenter, stepped-wedge cluster randomized interventional study in academic and peripheral hospitals in the Netherlands. All hospitals start simultaneously with a control phase in which standard care is provided. Sequentially, in a randomized order, hospitals cross over to the intervention phase in which patients at risk are routinely followed up by an anesthesia professional at postoperative days 1 and 3, aiming to detect and prevent or treat postoperative complications. We aim to include 5600 adult patients who are at high risk of developing complications. The primary outcome variable is 30-day postoperative mortality. Secondary outcomes include incidence of postoperative complications and postoperative quality of life up to one year following surgery.

Statistical analyses will be performed to compare the control and intervention cohorts with multilevel linear and logistic regression models, adjusted for temporal trends and for clusters (hospitals). The time horizon of the economic (cost-effectiveness) evaluation will be 30 days and one year following surgery.

**Discussion:**

TRACE is the first to study the effects of a routine postoperative visit by an anesthesia healthcare professional on mortality and cost-effectiveness of surgical patients. If the intervention proves to be beneficial for the patient and cost-effective, the stepped-wedge design ensures direct implementation in the participating hospitals.

**Trial registration:**

Nederlands Trial Register/Netherlands Trial Registration, NTR5506. Registered on 02 December 2015.

## Background

Perioperative complications occur in approximately 30–40% of non-cardiac surgical patients [1] and are the leading cause of early postoperative morbidity and mortality [2]. Moreover, the occurrence of early complications seems to be associated with long-term mortality that persists for years after surgery [3]. Several studies have demonstrated that surgical complications increase the overall cost of care [4–6]. Therefore, avoiding or even early treatment of complications is valuable in terms of cost-effectiveness [5, 7].

Although there is little variation in the occurrence of complications among hospitals, the resulting in-hospital mortality related to perioperative complications varies considerably [1]. In 1992, Silber et al. created the term failure-to-rescue to describe the percentage of deaths in relation to complications per surgical procedure [8]. Depending on the type of surgery, the failure-to-rescue rate varied widely across hospitals [9, 10]. Most likely, some organizations are able to cover the needs of patients with complications better than others [1, 8, 11, 12]. A more recent trial from the ISOS group observed a failure-to-rescue rate in the range of 1.7–3.6% in a mixed cohort of more than 44,000 patients in 27 countries [13].

Factors contributing to the development of failure-to-rescue have been studied intensely over the past 15 years; however, most of the data come from national or institutional databases and only little is known about failure-to-rescue rates in Europe [13]. It has been hypothesized that regular visits by highly educated and trained health professionals such as intensive care physicians, surgeons, or anesthesiologists can contribute to a decreased incidence of complications by earlier detection and adequate treatment.

Until now, no studies have been performed on the impact of routine postsurgical anesthesia visits on the incidence of postoperative complications. Therefore, we designed a nation-wide study in which patients at risk are routinely followed up by an anesthesia professional at postoperative days 1 and 3, aiming to detect and prevent or treat postoperative complications. Based on the available literature, we hypothesized that routine postsurgical anesthesia visits decrease the incidence of failure-to-rescue and reduce postoperative 30-day mortality by 50%.

### Research questions

What is the incidence of postoperative complications in this study cohort?Is there an impact of regular anesthesia visits on postoperative days 1 and 3 in reducing postoperative complications, 30-day mortality, and length of stay?What is the impact of the routine anesthesia visits on the time to implementation of rescue therapy, the utilization of high-care and intensive care facilities after complications, and the length of stay in these units?What is the impact of routine anesthesia visits on the quality of recovery 30 days after surgery and on the quality of life one year after surgery?Is the implementation of routine anesthesia visits after surgery cost-effective compared to standard postoperative care?

## Methods/Design

### Study design

The TRACE study is a multicenter prospective interventional study with a stepped-wedge design, aiming to recruit 5600 patients. In the beginning of the study all participating medical centers will provide perioperative care using the standard approach. All patients included during the standard approach period will be enrolled in the control group. Stepwise and at equal time periods, interventional postoperative anesthesia care will be implemented in the participating centers. The order in which the centers start with the intervention is randomized. The additional anesthesia care will consist of anesthesia visits on postoperative days 1 and 3 to follow up patient care and enhance rescue therapy when needed. By the end of the study, all participating centers will have implemented the intervention.

### Study schedule and randomization

Figure 1 shows the planned study schedule. Total recruitment time covers 31 weeks. All hospitals start in week 1 in the control phase and after week 8 sequentially cross over to the intervention phase. Between the two phases there is a one-week transition period (depicted with an *x*). In week 24, all hospitals will have started the intervention phase.

**Fig. 1 Fig1:**

Stepped-wedge schedule of the TRACE Study. Hospitals sequentially cross over from control phase to intervention phase. Transistion periods between phases are depicted by ‘x’

In total, 2800 patients will be recruited in the control phase and 2800 in the intervention phase. Each hospital will recruit 700 patients. The first hospitals to cross over (A–D) will recruit more patients in the intervention phase than in the control phase and the last hospitals (E–H) will recruit more patients in the control phase than in the intervention phase.

Randomization for the order in which hospitals cross over from the control phase to the intervention phase was performed before the first patient was recruited. The names of the eight hospitals were ordered randomly using envelope drawing. This randomized order was translated into the schedule presented in Fig. 1.

### Inclusion and exclusion criteria

#### Inclusion criteria

Patients undergoing elective surgery with an indication for postoperative hospital stay can be included in the study if they meet at least one of the following criteria:Aged ≥ 60 years;Aged ≥ 45 years with a revised cardiac risk index (rCRI) > 2;Aged ≥ 18 years with an indication for postoperative invasive pain therapy;Aged ≥ 18 years with a postoperative surgical APGAR-score (sAPGAR) < 5.

#### Exclusion criteria

Patients undergoing cardiac surgery and patients with an indication for a postoperative stay in the intensive care unit.

### Recruitment and consent

Patients will be recruited by a member of study team (anesthesiologist or research assistant) preoperatively, either during the preoperative screening or directly after hospital admission. Patients receive a written patient information letter and are additionally orally informed about the study aims and the study phase they will enter (control or intervention). If they agree to participate, they will be asked to sign informed consent.

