### Data collection

Patient and clinical data will be collected at several time-points during the study period: at inclusion (baseline); intraoperatively; postoperatively at days 1 and 3; during hospital stay; from hospital discharge until 30 days; and until 12 months. Data records will be coded and transcribed by local investigators into an Internet-based electronic case record form.

Data to be collected from patient record files include patient baseline characteristics, data on surgery and anesthesia, intraoperative adverse events, the postoperative clinical course, postoperative in-hospital adverse events, and post-discharge events measured at 30 days and at 12 months after the date of surgery. During the intervention period, data collection additionally includes anesthesia interventions on postoperative days 1 and 3.

Data will also be collected from patient questionnaires, completed at inclusion, seven days, 30 days, and 12 months postoperatively. The questionnaires include questions on quality of life (EuroQol Dutch EQ-5D-5 L), pain scores (numeric rating scale, NRS), functional recovery (Functional Recovery Index), and expected/perceived recovery (Global Surgery Recovery index). See Fig. 2 for an overview of enrolment, intervention, and assessments.

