### Statistical analysis

Primary and secondary outcome measures (proportions with 95% confidence intervals or means with standard deviations) will be calculated and presented in tables. A patient flow chart will be presented to account for inclusions per hospital and drop-out.

For the primary outcome and binary secondary outcomes, multi-level mixed effect logistic regression with random time by cluster interaction will be used to compare between the cohort that has not and the cohort that has received the intervention according to the stepped-wedge schedule. Time effects will be modelled according to appropriate methods, e.g. using spline functions. For continuous secondary outcomes, multi-level mixed effect linear regression will be used and for countable secondary outcomes, multi-level mixed effect Poisson regression models will be used. Analyses will be performed using SPSS and R.

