On cluster level, per-protocol analyses will be performed (i.e. if the intervention phase starts later than expected in a certain hospital, patients will be allocated to the control group until the hospital has actually crossed over). Once the intervention phase has started, individuals within that cluster will be analyzed according to the intention-to-treat principle. Adjustments will be made for temporal trends and for clusters within hospitals [17]. An economic evaluation from a hospital perspective will be performed for postoperative anesthesia follow-up of high risk surgical patients compared to standard postoperative care. The time horizon of the economic evaluation will be 30 days and one year following surgery. For reasons of efficiency, the analysis after one year will be performed in a subset of study participants. A cost-effectiveness analysis will be performed, based on the incremental costs per postsurgical visit. Standard sensitivity analysis will be performed to test whether results are robust for changing certain parameters, e.g. cost-prices. Confidence intervals surrounding the mean differential costs will be calculated by the bootstrap method. The latter will also be used to quantify the uncertainty surrounding the incremental cost-effectiveness ratio [18, 19]. Additionally, a budget impact analysis will be performed to assess the affordability of a routine postoperative visit by an anesthesia healthcare professional by relating the increase in cost due to investment in anesthesia professionals to the cost-savings due to the expected reduction in complications and hence length of hospitalization and mortality.

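### Patients learn their study phase before consenting, and the stated adjustment for time and hospital cannot correct a case-mix shift at crossover, so differential recruitment can bias the mortality comparison

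*Protocol article*

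**What the plan says.** Study schedule and randomization: "Randomization for the order in which hospitals cross over from the control phase to the intervention phase was performed before the first patient was recruited". Thus the order of the eight hospitals is fixed before any individual is approached.

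Recruitment and consent: "Patients will be recruited by a member of study team (anesthesiologist or research assistant) preoperatively". Patients receive written information and "are additionally orally informed about the study aims and the study phase they will enter (control or intervention". The next step is: "If they agree to participate, they will be asked to sign informed consent". Disclosure of the phase therefore comes before the decision to take part.

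Statistical analysis: for the primary outcome, "multi-level mixed effect logistic regression with random time by cluster interaction will be used", with time effects modelled, for example by splines. The same section says: "Adjustments will be made for temporal trends and for clusters within hospitals". The Methods part of the Abstract describes the models as "adjusted for temporal trends and for clusters (hospitals". No patient-level covariate is named in any of these places.

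Data collection: "Data to be collected from patient record files include patient baseline characteristics", together with data on surgery and anesthesia. Age and the revised cardiac risk index (rCRI) appear among the inclusion criteria.

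**The concern.** Randomising the order in which hospitals cross over protects the comparison only if the patients who enter do not depend on the phase. Here they can. The two phases offer different things (two extra visits by an anesthesia professional, or usual care), and both the patient and the person recruiting know which is on offer. Frail or anxious patients might accept more readily when visits are offered, and staff might approach different patients once the intervention is running.

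If so, control and intervention patients in the same hospital would differ in prognosis for reasons unrelated to the visits, and that difference would enter the primary odds ratio. About 84 deaths are expected in the whole trial, so a modest change in the share of high-risk patients could matter. Hidden benefit and spurious benefit are both possible, which leaves either result open to challenge.

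**Working it through.** **1. The plan's own figures.** Inputs from Sample size calculation: 2% against 1% mortality, alpha 0.05 (taken as two-sided), power 80%, ratio 1:1. With the pooled-variance formula for two proportions and no continuity correction:

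n per group = [1.960 × √(2 × 0.015 × 0.985) + 0.8416 × √(0.02 × 0.98 + 0.01 × 0.99)]² / 0.01² = 2319, total 4638.

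This matches the article exactly. 4638 × 1.2 = 5566, close to the stated 5600 (8 × 700). The sample size arithmetic is not in dispute.

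Expected deaths: 2800 × 0.02 + 2800 × 0.01 = 56 + 28 = 84.

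**2. Can the stated terms absorb a shift at crossover?**

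- A hospital effect is constant over time, so it cannot absorb a change within that hospital.
- A common time trend is shared by all hospitals, so it cannot absorb a change that falls at a different date in each.
- A random time-by-hospital term allows for deviations centred on zero. It does not remove a systematic shift that switches on together with the intervention indicator.

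A case-mix change that starts at each hospital's own crossover therefore coincides with the treatment term and is attributed to it.

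**3. Illustration A (all inputs assumed).** 20% of patients have 6% mortality and 80% have 1%: 0.20 × 6% + 0.80 × 1% = 2.00%. High-risk patients are under-enrolled in the control phase.

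- 20% shortfall: (0.16 × 6% + 0.80 × 1%) / 0.96 = 1.76% / 0.96 = 1.83%. Relative change: (2.00 − 1.83) / 2.00 = about 8%.
- 40% shortfall: (0.12 × 6% + 0.80 × 1%) / 0.92 = 1.52% / 0.92 = 1.65%. Relative change: (2.00 − 1.652) / 2.00 = 17.4%.

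This direction makes the intervention look worse than it is. The same shortfall in the intervention phase would make it look better.

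**4. Illustration B (different assumed inputs).** Control mortality is 2%, and 30% of control patients are high-risk with relative risk RR. The share becomes q in the intervention phase and there is no true effect. Intervention mortality = 2% × (1 − q + q × RR) / (0.7 + 0.3 × RR). Rejection is for a two-sided two-proportion z-test with 2800 per phase, ignoring clustering and time.

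| q | RR | Intervention mortality | Odds ratio | Rejection |
|---|---|---|---|---|
| 30% (no shift) | any | 2.00% | 1.00 | 5.0% |
| 27% | 2 | 1.95% | 0.98 | 5.2% |
| 20% | 3 | 1.75% | 0.87 | 10.6% |
| 20% | 5 | 1.64% | 0.82 | 17.5% |
| 35% | 2 | 2.08% | 1.04 | 5.5% |
| 40% | 5 | 2.36% | 1.19 | 15.4% |

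With a true halving of mortality, the crude power of 87% moves to between 69% (q = 40%, RR 5) and 96% (q = 20%, RR 5). The effect thus runs from negligible to serious, depending on inputs that the article cannot supply.

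**The case against.** The strongest reply is that a covariate list and a baseline table by phase usually belong in a statistical analysis plan. The article condenses a full protocol (version 5) that is not shown. It never says that time and hospital are the only adjustments. A reader might infer that patient covariates have been ruled out, but the text does not support that, and an unseen plan may include them. What stands is narrower. The article states what the comparison is adjusted for in two places, and that set does not answer a risk created by its own consent procedure. If another document already adds baseline risk, the texts need only be aligned.

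A reader might also infer that the mortality comparison is biased. The article does not show that: it contains no evidence that recruitment differed by phase. The mechanism is plausible, but its direction and size are unknown and every magnitude above is assumed. The low end of Illustration B is close to nothing.

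Two objections to the remedy also stand. First, rCRI is one of four alternative entry criteria, and a patient aged 60 or over qualifies without it. Data collection does not name it, nor any surgical risk category, so complete recording cannot be assumed. Second, age and surgery type do not measure frailty or anxiety, so adjustment removes only the measured part of any selection.

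**Conclusion.** The concern holds as a risk that the stated plan leaves uncorrected. Phase is disclosed before consent, recruitment follows the fixing of the hospital order, and the named adjustments cannot correct a within-hospital change in case mix at crossover. Differential recruitment can therefore bias the 30-day mortality comparison in either direction.

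The size is not known. On the assumed 20%/80% mix, a 20% or 40% shortfall of high-risk control patients gives a spurious relative change of about 8% or 17%. On the second set of assumptions, the odds ratio with no true effect lies between 0.82 and 1.19, and the false-positive rate between 5.2% and 17.5%. These figures show what could happen under the stated inputs and are not estimates for this trial. The point does not affect the planned number of patients.

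**What to change.** Prespecify in the primary mixed logistic model a short set of pre-surgical prognostic covariates from the data already collected:

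- age as a continuous variable;
- a coarse grouping of surgery type or specialty;
- rCRI, only if it is confirmed to be recorded for all patients.

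Keep the model with time and hospital only as a sensitivity analysis. Tabulate baseline risk by phase within each hospital, so that a shift at crossover can be seen. State that selection on unmeasured traits such as frailty or anxiety is not removed by this adjustment.

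Fix the set before outcomes are compared by phase, because covariates chosen after an imbalance has been seen would invite criticism. Under Trial status, recruitment was still incomplete at initial submission.

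The cost is wording plus a few parameters. With 3 to 5 added terms there would be 84 / 3 = 28 to 84 / 5 = about 17 expected deaths per added term. The model also carries time and hospital terms, so the surgery grouping must stay coarse. Age and surgery type should need no new data, and the sample size does not change.

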### Intervention and control condition

During the intervention phase, all participants will receive a postoperative visit from the anesthesiologist at postoperative days 1 and 3. The postoperative visit is standardized and based on the Modified Early Warning Score (MEWS). The MEWS includes the following measurements: respiratory rate; heart rate and rhythm; systemic oxygen saturation; systolic blood pressure; body temperature; level of consciousness; and urine output. Other measurements include: visual analogue score to assess pain during rest and movement; nausea/vomiting; defecation; and mobilization. In case of a higher MEWS score and/or other concerns, the anesthesia health professional will advise the treating physician on further diagnosis, treatment, and follow-up of the patient.

During the control phase, participants will receive standard care, without a standardized visit from the anesthesiologist. The treating physician may ask the anesthesiologist in consultation when deemed necessary. Standard of care may slightly differ across the different participating hospitals.

### Participating centers

The study will be performed in eight Dutch hospitals, representing general hospitals, tertiary referral hospitals, and academic centers. All participating hospitals received approval from the Board of Directors to participate in the TRACE study.

### Data collection

Patient and clinical data will be collected at several time-points during the study period: at inclusion (baseline); intraoperatively; postoperatively at days 1 and 3; during hospital stay; from hospital discharge until 30 days; and until 12 months. Data records will be coded and transcribed by local investigators into an Internet-based electronic case record form.

Data to be collected from patient record files include patient baseline characteristics, data on surgery and anesthesia, intraoperative adverse events, the postoperative clinical course, postoperative in-hospital adverse events, and post-discharge events measured at 30 days and at 12 months after the date of surgery. During the intervention period, data collection additionally includes anesthesia interventions on postoperative days 1 and 3.

Data will also be collected from patient questionnaires, completed at inclusion, seven days, 30 days, and 12 months postoperatively. The questionnaires include questions on quality of life (EuroQol Dutch EQ-5D-5 L), pain scores (numeric rating scale, NRS), functional recovery (Functional Recovery Index), and expected/perceived recovery (Global Surgery Recovery index). See Fig. 2 for an overview of enrolment, intervention, and assessments.

